#### **6.7. Treatment of Overdose**

Not applicable

## **6.8. Concomitant Therapy**

Supportive medications will be recorded in the eCRF ([Section 8.1](#)).

Systemic cancer treatment must be paused for one week prior to, during, and one week after the radiotherapy treatment.

Patients cannot be included in other interventional clinical trials until the 4-week follow-up assessment is completed.

## **7. Discontinuation of Study Intervention and Participant Discontinuation/Withdrawal**

### **7.1. Discontinuation of Study Intervention**

It may be necessary for patients in arm B to permanently discontinue study intervention (i.e. radiotherapy), ([Section 6.5](#)). If study intervention is permanently discontinued, the patient may remain in the study to be evaluated for the planned assessments if the patient has not withdrawn the written consent. See the SoA ([Section 1.2](#)) for data to be collected at the time of discontinuation of study intervention and follow-up and further evaluations.

#### **7.1.1. Temporary Discontinuation**

See [Section 6.5](#)

#### **7.1.2. Rechallenge**

See [Section 6.5](#).

### **7.2. Participant Discontinuation/Withdrawal from the Study**

- A patient may withdraw from the study at any time at his/her own request or may be withdrawn at any time at the discretion of the investigator for safety, behavioral, or compliance reasons. This is expected to be uncommon.
- At the time of discontinuing from the study, if possible, an early discontinuation visit should be conducted, as shown in the SoA. See SoA ([Section 1.2](#)) for data to be collected at the time of study discontinuation.
- The patient will be permanently discontinued from both the study intervention and the study at that time.
- If the patient withdraws the consent for disclosure of future information, the sponsor may retain and continue to use any data collected before such a withdrawal of consent.
- If a patient withdraws from the study, he/she may request destruction of any samples taken and not tested, and the investigator must document this in the site study records.

### **7.3. Lost to Follow-up**

A patient will be considered lost to follow-up if he/she repeatedly fails to return for scheduled visits and is unable to be contacted by the study site.

The following actions must be taken if a patient fails to return to the clinic for a required study visit:

- The site must attempt to contact the patient and reschedule the missed visit as soon as possible and counsel the patient on the importance of maintaining the assigned visit schedule and ascertain whether or not the patient wishes to and/or should continue to participate in the study.
- Before a patient is deemed as being lost to follow-up, the investigator or designee must make every effort to regain contact with the patient (when possible, telephone calls and, if necessary, a certified letter to the patient's last known mailing address or local equivalent methods). These contact attempts should be documented in the patient's medical record.
- Should the patient continue to be unreachable, he/she will be considered to have withdrawn from the study.

Discontinuation of specific sites or of the study as a whole is handled as part of [Appendix 1](#).

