**Brief Summary:**

The purpose of this study is to investigate whether palliative radiotherapy delivered 1-2 fractions of 8 Gy is non-inferior to palliative radiotherapy delivered in 5 fractions of 5 Gy with respect to change in patient-reported symptom intensity in patients with pelvic soft tissue tumors originating from either gastrointestinal, urological or gynecological cancer. Patients will define a target symptom as their main complaint according to study-specific predefined categories (pain, bleeding, bowel dysfunction, lower urinary tract dysfunction or vaginal dysfunction).

Patients will be randomly assigned to radiotherapy intervention with either 1-2 fractions of 8 Gy or 5 fractions of 5 Gy. Patients entering the study must be considered as candidates for palliative radiotherapy, and have a target symptom intensity at baseline of minimum 4 points on the NRS, which ranges from 0-10 with 0 indicating no symptom intensity and 10 indicating the worst symptom intensity imaginable.

For patients randomized to 1-2 fractions of 8 Gy, the second fraction will be offered if predefined criteria for unsatisfactory symptomatic response are met, assessed at the 4-week follow-up ([see Section 4.3.1](#)).

Assessment of endpoints will be performed at 4, 8, 12 (primary endpoint), 26 and 52 weeks after the radiotherapy is completed. Assessments include patient-reported evaluation of symptom intensity (NRS), QoL, overall patient satisfaction and physician-reported toxicities. Subjects will be followed with respect to overall survival until death, or censoring, defined as either loss to follow-up, study withdrawal or end of study.

The radiotherapy planning and deliverance, and the study-specific follow-up visits (attendance or by telephone) will be performed at the patients' local radiotherapy unit. Additional follow-up visits related to the patients' cancer disease will be performed at their local cancer department, and will be according to the institutional practice, independent of study inclusion.

Patients will be included over a period of 2-4 years with a maximum follow-up at study closure (overall survival).

The results of this study may contribute to the establishment of standard treatment recommendations, both nationally and internationally. Both interventions are currently being used in clinical practice, which will facilitate the implementation of study results.

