## 1.2. Schedule of Activities (SoA)

| Procedure                                                         | Up to 28 days |                | Intervention Period [1 or 5 weekdays] |    |    |    |    | Follow-up a |                       |                                    |                        |                         |                         | Notes                          |
|-------------------------------------------------------------------|---------------|----------------|---------------------------------------|----|----|----|----|------------------------|-----------------------|------------------------------------|------------------------|-------------------------|-------------------------|--------------------------------|
|                                                                   | Screening     | Preparation    | D1                                    | D2 | D3 | D4 | D5 | 1 week
+/- 3 days   | 4 weeks
+/- 4 days | 8 weeks
+/- 4 days b | 12 weeks
+/- 7 days | 26 weeks
+/- 2 weeks | 52 weeks
+/- 4 weeks |                                |
| Informed consent                                                  | X             |                |                                       |    |    |    |    |                        |                       |                                    |                        |                         |                         | Section 10.1.2 |
| Inclusion and exclusion criteria                                  |               | X              |                                       |    |    |    |    |                        |                       |                                    |                        |                         |                         | Section 5      |
| Demography and medical history                                    | X             |                |                                       |    |    |    |    |                        |                       |                                    |                        |                         |                         | Section 8.1    |

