## 4. Study Design

### 4.1. Overall Design

This is a prospective, randomized, open-label, national, parallel-arm non-inferiority phase III study designed to establish non-inferiority of radiotherapy with 1-2 fractions of 8 Gy to 5 fractions of 5 Gy (active comparator) with respect to patient-reported symptomatic relief. The study population includes patients with gastrointestinal, urological, or gynecological cancer considered as candidates for palliative radiotherapy due to symptomatic pelvic soft tissue tumors. Patients must have an expected survival beyond 12 weeks. Patients will be included over 2-4 years. Eligible patients identified in the screening period will be randomized to either arm A or arm B with an allocation ratio of 1:1 after collection of a signed informed consent. Study-specific baseline evaluation will be performed between date of signed informed consent and intervention start.

Patients in arm A will initially be treated with a single fraction of 8 Gy. In case of unsatisfactory symptom relief after 4 weeks of follow-up, a second radiotherapy fraction may be offered if at least one of the following two predefined criteria are met: 1)  $\leq 2$  point improvement on the NRS-scale and 2) initial symptomatic effect, but rapid deterioration ([Section 4.3.1](#)). Primary and secondary endpoints will be assessed after 4, 8, 12, 26 and 52 weeks of follow-up (last visit, toxicities only) after completed radiotherapy. Subjects will be followed with respect to overall survival until death or censoring (loss to follow-up, study withdrawal, or end of study).

The study timeline is presented in Figure 1.

[figure not shown]

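### Overall survival is censored when a patient is lost or withdrawn and no vital status is sought afterwards, so deaths after exit can be missed and a survival difference masked

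*Protocol*

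**What the plan says.** **Leaving the study.** Section 7.3 requires real effort before a patient is declared lost ("the investigator or designee must make every effort to regain contact with the patient"), and then rules: "Should the patient continue to be unreachable, he/she will be considered to have withdrawn from the study". Section 7.2 allows withdrawal at the patient's own request, or by the investigator on grounds of safety, behaviour or compliance. Either way the patient is out of both treatment and study from that point. Section 7.2 treats withdrawal of consent to future information as a separate matter.

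**Survival follow-up.** The Brief Summary in Section 1.1 follows patients for OS "until death, or censoring, defined as either loss to follow-up, study withdrawal or end of study", and Section 4.1 repeats the rule. Under Sections 8.2.2 and 4.4, OS is assessed at the last patient's last visit (LPLV). Section 9.4 bases the main OS analysis on the full-analysis set, and Section 9.5.3 uses Kaplan-Meier, log-rank and Cox methods.

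**Exit data.** For a patient who leaves, Section 7.2 says "if possible, an early discontinuation visit should be conducted, as shown in the SoA", and again sends the site to the SoA "for data to be collected at the time of study discontinuation".

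**The concern.** Kaplan-Meier, log-rank and Cox analyses assume that a censored patient has the same prognosis as those still followed, given any covariates in the model. Eligibility extends to ECOG 3 and to expected survival only just beyond 12 weeks, so it is reasonable to expect some losses of contact to reflect decline or death. If those patients are censored while they are in fact dying, the curves are too high. If the arms lose patients at different rates, the comparison is distorted.

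OS is a secondary endpoint, but it carries weight in the decision. Sections 2.1, 4.2 and 9.2 all make comparable OS part of the case for the short course. An error that makes the arms look alike is therefore the one to guard against.

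Separately, a site that looks up the early discontinuation visit in the SoA finds no description of it.

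**Working it through.** **1. The path of a patient who leaves.** An unreachable patient is counted as withdrawn (7.3), is off study (7.2), and is censored for OS (1.1, 4.1). A patient withdrawn by the investigator takes the same path from 7.2.

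**2. Routes by which a later death could reach the database.**
- Section 8.1 has eCRF items for off-study date and cause and for cause of death, but names no source once visits have stopped.
- Section 10.3.2 requires deaths within the follow-up period to be reported, but gives no means of learning of them after exit.
- Section 8.5.1 does not oblige investigators to look for events after participation ends. A later death is notified only if they hear of it and consider it related.

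None of these obtains vital status after exit.

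**3. The plan's own figures.** None depends on this point, and the sample size in Section 9.3 reproduces. With margin 1, SD 2, one-sided 2.5%, power 85% and a true difference of 0 (assumed, as none is stated), n per arm = 2 × (1.960 + 1.036)² × 2² / 1² = 71.8, so 72 per arm and 144 in total, against 146 stated. Power at 146 by the t test is 85.1%. Allowing for 25% exclusion, 146 / 0.75 = 194.7, so 195, against 200 stated. The plan thus tolerates 200 − 146 = 54 patients (27%) not evaluable. It does not split them between death, withdrawal, loss and other causes, so the number censored by these rules cannot be computed.

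**4. Illustration (all inputs assumed).** Let p be the share of an arm lost, S_r the 6-month survival of those kept, and S_l that of those lost.
- True survival = (1 − p) × S_r + p × S_l
- Kaplan-Meier reads about S_r, exactly so if those lost are censored before any death
- Overstatement ≈ p × (S_r − S_l)

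| p | S_r | S_l | True survival | Kaplan-Meier | Overstatement |
|---|---|---|---|---|---|
| 10% | 65% | 0% | 0.90 × 0.65 = 58.5% | about 65% | 6.5 points |
| 10% | 65% | 30% | 0.585 + 0.10 × 0.30 = 61.5% | about 65% | 3.5 points |
| 15% | 65% | 0% | 0.85 × 0.65 = 55.25% | about 65% | 9.75 points |
| 5% | 65% | 0% | 0.95 × 0.65 = 61.75% | about 65% | 3.25 points |

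If the last two rows are the two arms, the true difference is 61.75 − 55.25 = 6.5 points, while both curves read about 65%. If S_l equals S_r there is no bias.

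**5. The SoA.** Its columns are screening, preparation, D1 to D5, and weeks 1, 4, 8, 12, 26 and 52. No column, row or footnote describes a discontinuation visit.

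**The case against.** The strongest reply is that much of the safety net exists. Contact attempts are demanding, Section 7.2 expects withdrawal to be uncommon, deaths before exit are recorded, and patients remain under their local cancer department. The exact censoring date can be left to the SAP. All of this stands, and it limits the point to deaths after exit. It does not close the gap: a SAP cannot analyse deaths that nobody was asked to look up.

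The illustration is also open to attack, since nothing in the protocol gives a rate of loss, suggests that it differs between arms, or says how many of those lost die. That is correct, which is why the figures show a range and direction and are not an estimate.

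Several stronger readings are tempting but unsupported:
- *That counting unreachable patients as withdrawn is itself the error.* Loss to follow-up already censors OS, so the relabelling changes nothing. The weakness is the absence of vital status after exit.
- *That leavers yield no last symptom score and no death.* The early visit is still requested where possible, scores from visits already made exist, data collected before consent is withdrawn may be kept, and the eCRF records off-study date and cause. An unreachable patient could not attend such a visit in any case.
- *That about 50 of 200 patients are affected.* The 25% in Section 9.3 covers all exclusions and is not a loss-to-follow-up rate.
- *That unequal loss would create a false difference.* In the scenario above it hides a true one.
- *That the missing visit harms the primary result.* The main analysis uses modified PP set 1, which requires completed 4- and 12-week visits, so an exit score before week 12 would not enter it.
- *That Section 7.1 has the same broken reference.* It concerns stopping radiotherapy, after which patients may stay for planned assessments, and the scheduled visits largely serve it.

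**Conclusion.** The point holds in a limited form. As written, the protocol censors OS at loss to follow-up and withdrawal and has no means of finding deaths after exit, so censoring may be informative. The likely direction is overstated survival, with the possibility that a real difference between arms is masked. This matters because comparable OS is a condition for adopting the short course.

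The size is unknown. The 3.5 to 6.5 point range and the hidden 6.5-point difference rest wholly on assumed loss rates, an assumed 65% survival in the rest, and assumed poor survival among those lost. That patients leave because they are deteriorating is plausible, but the documents do not say so. No stated figure changes.

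The missing early discontinuation visit is a plain but minor cross-reference error affecting supportive data only.

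**What to change.** **Main change**, in Sections 7.2, 7.3, 1.1 and 4.1:
- State that loss of contact or investigator-initiated withdrawal ends study visits only.
- Take vital status and date of death from medical records until LPLV, unless the patient withdraws consent to further data. Section 3 already draws on medical records for clinical factors and costs.
- Censor patients without a recorded death at the last date known alive.

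**Minor change**, in Section 7.2 and the SoA: either add an early discontinuation visit with its assessments listed, or delete the reference.

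**Cost:** protocol wording and a records check at LPLV for the patients concerned. If the visit is kept, one SoA column and one eCRF visit are added.

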## 8. Study Assessments and Procedures

- Study procedures and their timing are summarized in the SoA ([Section 1.2](#)). Protocol waivers or exemptions are not allowed.
- Immediate safety concerns should be discussed with the sponsor immediately upon occurrence or awareness to determine if the patient should continue or discontinue study intervention.
- Adherence to the study design requirements, including those specified in the SoA ([Section 1.2](#)), is essential and required for the study conduct.
- All screening evaluations must be completed and reviewed to confirm that potential study participants meet all eligibility criteria. The investigator will maintain a screening log to record details of all patients screened and to confirm eligibility or record reasons for screening failure, as applicable.
- Procedures conducted as part of the patient's routine clinical management (e.g., blood count) and obtained before signing of the informed consent form may be utilized for screening or baseline purposes provided the procedures met the protocol-specified criteria and were performed within the time frame defined in the SoA ([Section 1.2](#)).

## 8.1. Baseline Demography and Current Medical History

The following medical history will be recorded in the eCRF;

- Birthyear
- Sex
- Smoking status
- ECOG performance status
- Preferred language (Norwegian or English)
- Cancer diagnosis and disease status (primary origin only, locoregional disease below common iliac artery, locoregional disease below aortic bifurcation, metastatic)
- Histology and date of diagnostic/initial tumor biopsy
- Date of other (most and second most recent) tumor biopsies if performed
- Target symptom (indication for radiotherapy) and patient-reported symptom intensity
- Relevant comorbidity
- Concomitant supporting medications
  - Pain medication, opioid and non-opioid, invasive
  - Tranexamic acid
  - Anticoagulants
  - Laxatives
  - Antidiarrheal medication
  - Steroids
  - Antiemetics
- Systemic cancer treatment ongoing or in close proximity (withinlast 6 weeks)

- Relevant medical occurrences that begin before the start of study intervention but after obtaining informed consent. Relevant medical occurrences include those of possible impact on either of study endpoints (e.g. symptomatic effect, toxicities, QoL)
- Prior radiotherapy with overlapping radiotherapy field (re-irradiation)
- Baseline blood tests
- Date of prior MRI of tumor areas if performed
- If off study, date and cause
- If dead, cause of death
- If dead to other than cancer progression, autopsy performed

## 8.2. Efficacy Assessments

Planned time points for all efficacy assessments are provided in the SoA ([Section 1.2](#)).

### 8.2.1. Patient Reported Outcome Measures

#### 8.2.1.1. Symptom Intensity

Patients will have a target symptom as indication for radiotherapy. Target symptom is the patients main complaint, and will be organized into five predefined categories (pain, bleeding, bowel dysfunction, lower urinary tract dysfunction, vaginal dysfunction). If present, two additional symptoms may be assessed.

Symptom intensity will be reported at baseline as part of clinical routine for decision regarding radiotherapy indication. Patients may require supportive medication adjustments to relieve symptoms pending on radiotherapy. Symptom intensity must be assessed *before* such adjustment, and adjustments shall be performed without any delay.

Symptom intensity will further be assessed after 4, 8, 12 and 26 weeks of follow-up.

Supportive medication corresponding with NRS at all timepoints will be recorded in the eCRF.

Symptom intensity will be measured on a NRS ranging from 0-10, where 0 (no symptom intensity) to 10 (worst symptom intensity imaginable). The following will be measured:

- Average symptom intensity the last 24 hours (primary endpoint)
- Maximum symptom intensity the last 24 hours
- Minimum symptom intensity the last 24 hours

Patients referred from hospitals without radiotherapy might have required adjustments in supportive medications prior to evaluation at the radiotherapy unit. Hence, these adjustments were performed before the patient was considered eligible for study inclusion, but may have reduced target symptom intensity below the limit for inclusion ( $\text{NRS} \geq 4$ ). In these cases, the target symptom intensity prior to adjustments in supportive medications may be registered as baseline NRS as long as registered supportive medications corresponds

#### **8.2.1.2. EORTC QLQ-C15 PAL**

The European Organization for Research and Treatment of Cancer Quality of Life Questionnaire- Core15-PAL.

Assessed at baseline and after 4, 8, 12 and 26 weeks of follow-up

#### **8.2.1.3. PGIC 7-point scale**

Patient global impression of change assessed on a 7-point scale.

Assessed after 4, 8, 12 and 26 weeks of follow-up.

### **8.2.2. Overall Survival**

Will be assessed at the end of the study defined as LPLV.

### **8.2.3. Health economics**

The 5 Level-EuroQol-5 Dimension (EQ-5D-5L) assessed at baseline and after 4, 8, 12 and 26 weeks of follow-up.

Costs related to attendance at the radiotherapy unit, transportation and hospitalization (including coding)

## **8.3. Safety Assessments**

Planned time points for all safety assessments are described in the SoA ([Section 1.2](#)).

### **8.3.1. Follow-up after 1 week**

A follow-up after one week for assessment of AEs ( $\geq$  grade 3) and SAEs will be performed.

Patients will have daily contact with radiation therapists at the radiotherapy unit during the study intervention for reporting of toxicities and other complaints.

### **8.3.2. Physician-assessed toxicity CTCAE**

Common Terminology Criteria for Adverse Events version 5.0.

Assessed baseline and after 4 weeks, 12 weeks and 52 weeks of follow-up.

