Abbreviations: AE=Adverse Event, CT= Computed Tomography, CTCAE= Common Terminology Criteria Adverse Events, CRP= C-reactive protein, ECOG = Eastern Cooperative Oncology Group, EORTC QLQ-C15 PAL= European Organization for the Research and Treatment of Cancer Quality of Life Questionnaire-Core15 Palliative, GPS= Glasgow Prognostic Score, LDH=Lactate dehydrogenase, NRS=Numerical Rating Scale, SAE=Serious Adverse Event, WOCBP=Women of childbearing potential

a All follow-up is defined from the day of completed radiotherapy (arm A: D1, arm B: D5 or D6-10 if modifications, see Section 6.5)

b If a second fraction is offered (see [Section 4.3.1](#)), evaluation must be scheduled 4 weeks +/- 4 days after the second fraction is delivered,. For all other patients, evaluations must be scheduled 8 weeks +/- 4 days from baseline

c Within 72 hours before randomization

d Only if baseline NRS score of target symptom is available

e Including pain medication, tranexamic acid, anticoagulants, laxatives, antidiarrheal medication, antiemetics and steroids

f Radiotherapy treatment within the same planning target volume (PTV) (additional fraction after 4 weeks in arm A is not considered reirradiation)

g I.e. hospital submissions and coding record related to radiotherapy

h All AE ≥grade 3/SAE

i Only AE ≥grade 3/SAE with suspected causality with radiotherapy

j To be performed within 4 days after decision

k Only if second fraction is offered. See [Section 4.3.1](#)

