#### **8.5.1. Time Period and Frequency of Collecting AE and SAE Information**

All SAEs and AEs with CTCAE grade  $\geq 3$  will be collected from the start of study intervention until the 52 week follow-up visit as specified in the SoA ([Section 1.2](#)), and recorded in the eCRF. After the 4 week follow-up visit, only SAEs/AEs with CTCAE grade  $\geq 3$  with probable/definite causality with radiotherapy will be reported. For patients in arm A receiving a second radiotherapy fraction, all SAEs/AEs with CTCAE grade  $\geq 3$  will be reported until the 8 week follow-up.

Medical occurrences that begin before the start of study intervention, but after obtaining informed consent will be recorded as current medical history ([section 8.1](#)), and not as AEs.

All SAEs will be recorded and reported to the sponsor or designee immediately and under no circumstance should this exceed 24 hours, as indicated in [Appendix 3](#). The investigator will submit any updated SAE data to the sponsor within 24 hours of it being available.

Investigators are not obligated to actively seek information on AEs or SAEs after conclusion of the study participation. However, if the investigator learns of any SAE, including a death, at any time after a patient has been discharged from the study, and he/she considers the event to be reasonably related to the study intervention or study participation, the investigator must promptly notify the sponsor.

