#### Assessment of Intensity

The investigator will make an assessment of intensity for each AE and SAE reported during the study using the National Cancer Institute Common Terminology Criteria for Adverse Events (CTCAE) v 5.1). If an AEs or an SAEs are not covered by CTCAE, it will be assigned to 1 of the following categories:

- Mild: An event that is easily tolerated by the participant, causing minimal discomfort and not interfering with everyday activities.
- Moderate: An event that causes sufficient discomfort to interfere with normal everyday activities.
- Severe: An event that prevents normal everyday activities. An AE that is assessed as severe should not be confused with an SAE. Severe is a category utilized for rating the intensity of an event; and both AEs and SAEs can be assessed as severe.

An event is defined as 'serious' when it meets at least 1 of the predefined outcomes as described in the definition of an SAE, NOT when it is rated as severe.

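### Two-fraction patients in arm A have no scheduled all-grade CTCAE grading about 4 weeks after their last fraction, whereas arm B does

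*Protocol*

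**What the plan says.** **Grading schedule.** Section 8.3.2 sets physician CTCAE grading: "Assessed baseline and after 4 weeks, 12 weeks and 52 weeks of follow-up". The CTCAE row of the Schedule of Activities (Section 1.2) agrees and has no mark at 8 weeks.

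**Clock.** Footnote a of the Schedule: "All follow-up is defined from the day of completed radiotherapy (arm A: D1"; arm B counts from its last fraction. The origin for arm A does not move when a second fraction is given.

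**Second fraction.** Under Section 4.3.1 it may be offered at the 4-week visit. Footnote j on its timing: "To be performed within 4 days after decision". Footnote b then re-times the 8-week visit only: "evaluation must be scheduled 4 weeks +/- 4 days after the second fraction is delivered".

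**What the re-timed visit collects.** It collects patient-reported outcomes and, for second-fraction patients only, an AE/SAE review limited by footnote h: "All AE ≥grade 3/SAE". Section 8.5.1 matches this. Its rule begins "For patients in arm A receiving a second radiotherapy fraction, all SAEs/AEs with CTCAE grade" and continues with grade 3 or higher, up to the 8-week follow-up. Appendix 3 adds: "The investigator will make an assessment of intensity for each AE and SAE reported during the study". Whatever is reported is therefore graded, but grade 1-2 events are not among the events collected there.

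**Use of the data.** Bladder and bowel toxicity at 4, 12 and 52 weeks is a secondary endpoint for the 1-2 fraction schedule (Section 3). Section 9.5.3 plans between-arm counts that separate grade 1-2 from grade 3-4. Section 9.2 makes comparable toxicity at 12 weeks one condition for recommending 1-2 fractions as standard of care.

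**The concern.** The protocol recognises that a second fraction needs its own early check. It moves a visit to 4 weeks after that fraction and reopens unrestricted reporting of events of grade 3 or higher until then. The all-grade form that feeds the secondary endpoint was not carried to that visit.

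As a result, toxicity about 4 weeks after the last dose is read in arm B and in single-fraction arm A patients, but never in two-fraction patients. Those patients have the arm A normal-tissue dose closest to arm B. Mild bladder or bowel effects of the second fraction that settle before week 12 may leave no trace in the endpoint data. An analysis plan cannot supply a reading that was not taken.

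**Working it through.** **The plan's own dose figures (Section 6.1, normal tissue, α/β = 3).** EQD2 = total dose × (dose per fraction + 3) / (2 + 3).
- One fraction: 8 × 11 / 5 = 17.6 Gy.
- Two fractions: 16 × 11 / 5 = 35.2 Gy.
- Arm B: 25 × 8 / 5 = 40 Gy.

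All three agree with the protocol's table.

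**Inputs for the timing check (Schedule of Activities; D1 of arm A = day 0).**
- Week 4: 28 ± 4 = day 24-32.
- Week 12: 84 ± 7 = day 77-91.
- Week 52: 364 ± 28 = day 336-392.
- Second fraction: decided at the week-4 visit and given 0-4 days later.
- Re-timed 8-week visit: 28 ± 4 = 24-32 days after the second fraction.

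**Day of the second fraction.** Earliest 24 + 0 = 24; latest 32 + 4 = 36.

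**Days from the second fraction to the next all-grade form (week 12).** Shortest 77 − 36 = 41; longest 91 − 24 = 67; nominal 84 − 28 = 56.

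**Days from the second fraction to week 52.** 336 − 36 = 300 to 392 − 24 = 368.

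**Days from last protocol fraction to each scheduled all-grade form**

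| Patients | First form | Second form | Week 52 |
|---|---|---|---|
| Arm B | 24-32 | 77-91 | 336-392 |
| Arm A, two fractions | none until week 12: 41-67 | – | 300-368 |

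The 41-67 window starts 41 − 32 = 9 days after arm B's first window ends and stops 77 − 67 = 10 days before arm B's second begins. The week-52 windows overlap.

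**With grading added at the re-timed visit.** Two-fraction patients would be read 24-32 days after their last fraction, the same window as arm B at week 4. From D1 that is 24 + 24 = day 48 to 36 + 32 = day 68. This is at least 77 − 68 = 9 days before any week-12 visit, so the two readings stay distinct.

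**How many patients.** The protocol does not state the share given a second fraction. With 146 / 2 = 73 evaluable patients in arm A, an assumed share of 10% to 50% gives about 7 to 37 patients. The amount of grade 1-2 toxicity missed cannot be derived from the protocol.

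**The case against.** The strongest reply is that nothing here is contradictory. Every section gives the same 4-, 12- and 52-week grading. Arm A is a strategy, one fraction with an optional second, and comparing strategies on a fixed clock is legitimate; a different interval since the last fraction is part of the strategy. **This stands.** The 12-week comparison needs no repair, but it does not supply the missing early reading.

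Second, the loss depends on a form that is not shown. If the week-12 form asks about the whole interval since the previous visit, grade 1-2 events after the second fraction would be caught, subject to recall over 41-67 days. **This stands in part.** The protocol does not state a look-back, and recall would reduce the gap but not close it.

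Third, short-lived mild events are missed in arm B too. Section 8.3.1 sets "A follow-up after one week for assessment of AEs" only at grade 3 or higher, plus SAEs, so grade 1-2 events that resolve before week 4 are lost in both arms. **This stands**, and it is one reason not to claim a direction.

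Fourth, patient-reported scores are taken at 8 weeks. They give some information where the symptom is bowel or urinary, but they are not physician CTCAE grades and do not enter this endpoint.

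A reader might infer that the gap flatters arm A, or that the second fraction is given without safety follow-up. The documents support neither. Events that clear before week 12 would be missed in arm A. Yet at week 12 two-fraction patients are nearer their last dose than arm B (nominally 56 against 84 days), which works against arm A. Events of grade 3 or higher and SAEs are collected at the re-timed visit.

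**Conclusion.** The point holds in a limited form. Arm A patients given the protocol's second fraction have no scheduled all-grade grading about 4 weeks after it. Their first is 41-67 days later, against 24-32 days after the last fraction in arm B. Grade 1-2 bladder and bowel toxicity of that fraction may be under-recorded.

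This rests on the second fraction being decided at the 4-week visit and given within 4 days, as the protocol states, and on visits keeping to their windows. It concerns only the protocol's own second fraction, not the further radiotherapy that Section 6.6 allows in both arms after week 4. Neither the number of patients affected nor the size or direction of any effect on the comparison can be established from the protocol.

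It would go too far to say that the 12-week toxicity comparison is invalid, or that the condition in Section 9.2 cannot be assessed. All-grade grading takes place in both arms at 12 weeks, and the protocol nowhere requires matched time since the last fraction. The primary endpoint, the sample size and the intended single-fraction reading at 4 weeks are untouched. This is a worthwhile and inexpensive improvement to data collection.

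**What to change.** **Data collection (Schedule of Activities and Section 8.3.2).** Add all-grade CTCAE grading of bladder and bowel for second-fraction patients at the re-timed 8-week AE/SAE review they already attend. Other patients need no new contact.

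**Analysis (Section 9.5.3).** Add a supportive between-arm comparison of bladder and bowel grade 4 weeks after the last protocol fraction, with one reading per patient:
- arm B and single-fraction arm A: the week-4 form;
- two-fraction arm A: the re-timed 8-week form.

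With one reading each, arm A gets no extra look in this comparison. Keep the fixed 4-, 12- and 52-week analyses as they are, and do not feed the added form into their event counts.

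**Cost.** A small amendment and a few extra items at an existing review, for second-fraction patients only. Those already past that visit will have no such reading, and their number should be reported with the comparison. The primary endpoint and sample size do not change.
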